## Abstract

**Background:**

Universal, high-quality childcare offers a unique opportunity to prevent developmental trajectories leading to mental health problems. Yet, growing evidence has shown that the process quality of Norwegian childcare centers varies considerably, and that research-based models for quality building are significantly lacking.

**Objective:**

To examine whether a model for quality building in childcare centers, Thrive by Three, increases the quality of child–caregiver interactions, and promotes child development, well-being, and mental health.

**Methods:**

The Thrive by Three study is a clustered randomized controlled trial involving 187 toddler groups in childcare centers across 7 municipalities within southern and central Norway. Each center is randomly allocated to the intervention or wait-list control group. Data are collected at 4 points: preintervention (T1), midway (T2), postintervention (T3), and 1-year postintervention (T4). Primary outcomes are changes in childcare quality measured by the Classroom Assessment Scoring System toddler version (CLASS), Student–Teacher Relationship Scale, Short Form (STRS-SF), and Life in Early Childhood Programs (LECP), as well as child development and mental health measured by The Brief Infant Toddler Social and Emotional Assessment (BITSEA, parent and teacher report), the Caregiver–Teacher Report Form (C-TRF), and Child Behavior Checklist (parent report) from the Achenbach System of Empirically Based Assessment (ASEBA) from 1.5 to 5 years, and child well-being measured by the Leiden Inventory for Child’s Well-Being in Day Care (LICW-D). Secondary outcomes are child cortisol levels, assessed in a subsample of 372 children.

**Results:**

As of August 2020, a total of 1531 children and 769 staff from 187 toddler groups were recruited. Because of turnover, the recruitment of staff will be ongoing until August 2020. As of January 2020, the intervention group has been working with Thrive by Three for 1.5 years. Data at T1, T2, and T3 from both the intervention and control groups have been completed and T4 will be completed in August 2020.

**Conclusions:**

This study makes an important contribution to the field of quality building in childcare centers. The results will provide greater insight into how high quality can be obtained and the effects of high-quality early childcare on child mental health. This in turn will be significant for policymakers and to the Norwegian society at large.

**Trial Registration:**

ClinicalTrials.gov NCT03879733; https://clinicaltrials.gov/ct2/show/NCT03879733 and Norwegian Research Council 260624/H10; https://prosjektbanken.forskningsradet.no/#/project/NFR/260624/Sprak=en

**International Registered Report Identifier (IRRID):**

DERR1-10.2196/17726

## Introduction

### Background

Mounting evidence supports the notion that high-quality childcare centers promote children’s mental health [1,2]. High-quality childcare protects and promotes the underpinnings of mental health in a phase of life when brain plasticity is most pronounced [3,4]; hence, it may prevent the onset of deviant developmental trajectories in toddlers and compensate for insufficient resources at home [5,6]. Evidence also suggests that centers of poor quality can have detrimental effects on children’s development [7,8]. Because more than 80% of 1 and 2 year olds in Norway attend childcare, and stay there for long hours [9], interventions targeting caregiver–child interactions may prove an important avenue toward universal prevention of mental health problems.

Childcare quality includes elements of both structure (eg, number of staff, staff training and education, group size, child-to-caregiver ratio) and process (eg, caregiver–child relationship, parental involvement) [10]. *Process quality* in terms of warm, sensitive, and stimulating relationships between caregivers and young children [11] is arguably the most important ingredient of quality as it has long-term effects on children’s mental health, well-being, and development [12]. Importantly, high process quality seems to be particularly important for children at risk [13].

New evidence shows that quality varies substantially between centers [14,15], and preliminary findings indicate that, by international comparison, quality in Norway is only moderately high [15]. Norway has failed to implement a minimum level of training for all childcare staff. As much as 60% of childcare staff have no formal qualifications on bachelor level for working with children [16]. Even some educated childcare teachers report lack of competence in taking care of children under the age of 3 [17]. This means that many toddlers spend most of their time interacting with staff with minimal or insufficient training. The need to enhance competence among childcare staff working with the youngest children is urgent. Moreover, a standardized and systematic procedure for measuring and monitoring process quality in childcare centers is lacking in Norway. This means that, unless a childcare center has participated in research, the level of quality that childcare centers provide to young children is largely unknown.

Few of the existing interventions for preventive quality improvement in childcare specifically focus on the youngest children. Furthermore, most interventions have been narrow in their scope, targeting only single topics such as conduct problems [18], anxiety [19], or language problems [20], thereby limiting their effect on children’s mental health. We will therefore break new grounds by conducting a cluster randomized controlled trial (RCT) of a newly developed comprehensive intervention for promoting mental health among toddlers through quality-enhancement in childcare, the *Thrive by Three* [21-23].

Thrive by Three is grounded in transactional models for development [24,25] and research showing that interactions between young children and caregivers are primary mechanisms of mental health, child development, and learning [26-29]. Thrive by Three is culturally sensitive, and is universally preventive in the sense that it includes all 1-3 year olds attending childcare. The intervention consists of 3 core elements: (1) quality building through competence enhancement for all staff regardless of level of formal education, (2) a model for peer-driven quality control and tailored supervision at classroom level in the participating centers, and (3) supervision of supervisors and mentors. Thrive by Three is modeled after the *Thrive by Five*, *Seeds to Success*, and *Early Achievers* quality-building and quality control measures, broadly implemented in childcare centers in the state of Washington in the United States [21-23] and piloted in a large Norwegian community sample [30].

This study has 2 primary aims: to determine the extent to which Thrive by Three (1) improves the quality of caregiver–child interactions and (2) strengthens children’s mental health, and social and cognitive development, after the intervention and at a 12-month follow-up. The secondary aims consist of determining the extent to which the intervention effects are moderated by (1) the implementation outcomes (fidelity and acceptability) and (2) child and family characteristics such as temperament, ethnicity, and socioeconomic background. In a subsample, we will also address (1) the characteristics of children with especially high cortisol levels during transition to childcare and (2) whether children in childcare units receiving the intervention have lower cortisol levels compared with controls. In another subsample we will qualitatively investigate parents’ and caregivers’ experience with the intervention.

### Pilot Study

The Thrive by Three intervention was piloted in a large community sample in 2 cohorts of 25/49 public (51%) and 24/49 private (49%) childcare centers from August 2016 to June 2018. A total of 49 centers and 243 groups of children aged 1-5 participated. The design was a simple pre–post design. The childcare centers were observed with Classroom Assessment Scoring System (CLASS; toddler and Pre-K), before the intervention started (pre) and after 10 months (post). Childcare staff filled out electronic questionnaires on background factors of the centers, the childcare classrooms, and themselves (ethnicity, education, staff turnover, attitudes toward the intervention). The pilot intervention differed from the current version of Thrive by Three intervention in 2 ways:

The written material given to the staff was less comprehensive in the pilot and parents were not given any written material.The staff supervisors did not receive supervision from mentors.

For toddler groups (ages 1-3) we found a small but significant increase in quality from pre to post in the Emotional and behavioral support domain (mean 5.97 [SD 0.41] vs mean 6.08 [SD 0.38]; *t*_103_=–2.45; *P*=.02) but not in the Engaged support for learning domain (mean 3.24 [SD 0.76] vs mean 3.44 [0.77]; *t*_103_=–1,86; *P*=.07). For the Pre-k groups (ages 3-5), there was a significant increase in quality from pre to post measures across all 3 domains: Emotional support (mean 6.06 [SD 0.56] vs mean 6.20 [SD 0.43]; *t*_127_=–2.56; *P*=.01), Classroom organization (mean 5.27 [SD 0.76] vs mean 5.55 [SD 0.66]; *t*_127_=–3.38; *P*=.001), and Instructional support (mean 2.67 [SD 0.84] vs mean 3.02 [SD 0.98]; *t*_127_=–3.40; *P*=.001). Moreover, qualitative interviews with center leaders, head teachers, and staff from the first cohort (N=53) revealed great satisfaction with the quality-building framework and the holistic approach to quality building. Overall, they reported feeling more competent in their day-to-day interactions with the children and highlighted that the intervention had given all staff on different levels shared knowledge and a shared language to talk about quality with colleagues. There were, however, also several challenges. Most importantly, staff needed more time than predicted to fully comprehend the CLASS framework and content of the specific dimensions. The supervisors did not receive enough support and reported lacking a manual/written material to help structure the supervision throughout the intervention period.

## Methods

### Study Design

This study is a clustered RCT delivered in childcare centers with toddler groups in 2 regions in Norway: southern and central. We selected a random sample using SPSS (IBM). The stages of enrollment, intervention, and assessment are presented in Table 1. A more detailed display of the different assessment time points is presented in Table 2.

**Table 1 table1:** The stages of enrollment, intervention, and assessment of Thrive by Three.

Research stage		Study period						
		Spring 2017	Fall 2017	Spring 2018	Fall 2018	Spring 2019	Fall 2019	Spring 2020
Enrollment								
Municipalities		x						
**Informed consent**								
	Staff	x	x					
	Children		x	x				
Allocation			x					
**Intervention**								
	Intervention group				x	x		
	Control group						x	x
**Assessment**								
	Primary and secondary outcomes				Pre	Post		1-year follow up

**Table 2 table2:** Overview of assessment and informants at different time points.

Assessment and informants		Time point			
		T1 (September 2018)	T2 (January 2019)	T3 (June 2019)	T4
**Questionnaires**					
	Childcare staff about their job	x		x	x
	Childcare staff about the child	x		x	x
	Parents about themselves and child	x		x	x
CLASS^a^ observations		x	x	x	x
Cortisol measurement (300 children)		x	x	x	

^a^CLASS: Classroom Assessment Scoring System.

### Eligibility Criteria

Childcare settings with toddler groups in the Oslo region and Central Norway are eligible for participation. The participating children must be aged between 12 and 35 months. Childcare center eligibility is determined by region of the country and municipality. The primary study sites are in southeastern and central parts of Norway. The recruitment period started in February 2017 and lasted until August 2018. First, municipalities were recruited during the spring of 2017. Then, childcare centers within each municipality were recruited during spring and fall of 2017. Childcare staff consented during the fall of 2017. Children were recruited from fall of 2017 until August 2018. The long recruitment period of children is due to the fact that children under the age of 2 typically enter childcare centers for the first time in August, the year they turn 1. The lists of eligible children were therefore not complete until August 2018. Because of a high staff turnover, new staff members are invited to consent to participate throughout the year.

The intervention is offered during a complete year cycle in the participating centers. The control group is offered the intervention the following year cycle. Childcare quality is measured before, during, and after the intervention (3 time points). Parents and staff fill out questionnaires before and after the intervention. In addition, participating toddler groups and children will be measured 1 year after the intervention to identify possible long-term effects.

Children in the participating toddler groups are recruited via a written invitation to their parents given to them at the childcare center. Childcare staff keep in touch with the parents throughout the study period. The project team has no direct contact with parents. All information is given through the childcare center.

### Inclusion Criteria

All childcare centers in the participating municipalities were allowed to participate as long as they had at least one toddler group, or groups with children aged 12–36 months. After the municipalities had consented to participate in the study, childcare centers within each municipality were recruited. Childcare centers volunteered to participate. All parents of children in the toddler groups of the participating childcare centers were invited to participate.

### Exclusion Criteria

Childcare centers with no children under the age of 36 months were not eligible for the study.

### Intervention Care and Comparison

#### Intervention

Thrive by Three is a 10-month intervention, aimed at increasing the quality of Norwegian childcare centers. It is grounded in transactional models for development [24,25] and research showing that interactions between young children and caregivers are a primary mechanism of mental health, child development, and learning [26-29].

Thrive by Three offers a standardized measurement of quality 3 times throughout the year through observations conducted by 25 certified observers (from the municipality) in classrooms with children between 1 and 3 years of age using a standardized observations method, CLASS toddler. Following observations, all staff in the intervention group receive feedback on a group level on their score based on the 8 quality dimensions of CLASS, showing strengths and weaknesses of interaction. Staff receive systematic guidance by their head teacher on a monthly basis based on the quality measure and an action plan for improvement. The head teachers, in turn, receive supervision from mentors. Staff in each toddler group meet together 10 times with their head teacher during the intervention period, focusing on 1 or 2 CLASS dimensions each time. Between meetings, all employees focus on the present CLASS dimension in their daily work with children.

All childcare employees in the 7 municipalities attend 3 full-day seminars, focusing on research-based knowledge on young children’s mental health and its risk and protective factors, early signs of mental and developmental problems, and crucial aspects of childcare quality. Center leaders and head teachers participate in 2 extra sessions focusing on leadership, feedback, supervision, and how to address concerns about a child to his/her parents when necessary.

In addition, comprehensive written material is provided to parents, employees, head teachers, and mentors. There are 7 booklets for parents about children’s early development and tips to help them support their own child’s development, guidance manuals for mentors, and a 30-page resource booklet for all employees in the centers. Access to the project website is also available to parents and employees at tf3.no.

#### Control

The wait-list control group is offered the intervention 1 year later but is observed at T1, T2, and T3 along with the intervention group. The control group does not receive feedback or guidance following the observations until they receive the intervention 1 year later.

### Procedure

#### Overview

Figure 1 presents a graphic representation of the study procedures. Following recruitment, observers and mentors are trained in the childcare quality observation method, CLASS [31]. This is a 2-day training, led by a certified trainer. After training, the Teachstone reliability test is taken. Supervisors get extra training in the method, but do not go through the reliability test to become certified. Each childcare unit is observed by the CLASS-certified observers for 45 minutes, preintervention, midintervention, and postintervention and at 1-year follow-up. The preintervention CLASS observation is used as the basis for supervision and quality enhancement in each unit.

**Figure 1 figure1:**
[figure not shown]
Flowchart of study procedures for Thrive by Three.

#### Randomization

Childcare centers within each municipality are randomly allocated to the intervention or wait-list control group. Because we could not randomize the units in the same center due to contamination, randomization occurred on the center level, but the intervention is on the unit level. The randomization was stratified based on center size to assure that larger and smaller centers were equally distributed across the control and intervention conditions.

#### Blinding

Because of the nature of the intervention, it is not possible for the participants to be unaware of the intervention condition they are assigned to.

### Outcomes

#### Data Collection

Data are collected at four points: T1 (preintervention), T2 (midway assessment), T3 (postintervention), and T4 (1-year postintervention follow-up). Participants from the intervention and control centers (parents, childcare staff, and group leaders) are sent links to the questionnaire via SMS text message or email. Each child is given unique, confidential identifiers to log-in and answer questions about the child (by the parent/staff). Both parents and 1 selected staff member working with each participating child are asked to fill out the questionnaires about the child. In addition, parents and childcare staff answer questions about themselves, and the staff about aspects of the center they work in. Each unit in the participating centers (both intervention and control centers) is also observed by trained CLASS observers at the following periods: preintervention, midintervention, postintervention, and during a follow-up 1 year later (only the intervention group).

T1 took place in September and October 2018 with CLASS observations in 187 units (both the control and intervention groups, with only the intervention group receiving feedback) and questionnaires to all staff and parents. T2 took place in January 2019 with new CLASS observations but no questionnaires. T3 took place at the end of the intervention (1 childcare year) in May/June 2019 with CLASS observations and questionnaires to all staff and parents. In addition, qualitative interviews will be conducted at T3. At 1-year follow-up after the intervention (T4) the intervention group is observed with CLASS and questionnaires will be filed out by all staff and parents (Textbox 1).

Study outcomes and measures used for Thrive by Three.
**Primary outcomes**
Childcare quality:Classroom Assessment Scoring System (CLASS) toddler versionThe Student–Teacher Relationship Scale, Short Form (STRS-SF)Life in Early Childhood Programs (LECP)Child outcomes:The Brief Infant Toddler Social and Emotional Assessment (BITSEA, parent and teacher report)Caregiver–Teacher Report Form (C-TRF, teacher report)Child Behavior Checklist (CBCL, parent report)Language Development Survey (LDS)Leiden Inventory for Child’s Well-Being in Day Care (LICW-D)Secure Base Safe Haven Observation Unit (SBSHO)
**Secondary outcomes**
Measurement of child cortisol levels

#### Primary Outcomes

##### Study Hypothesis

The primary outcome for this study is a comparison between centers randomly allocated to the Thrive by Three intervention and wait-list control centers receiving the intervention 12 months later. We hypothesize that Thrive by Three will prove superior to the wait-list control after the 10-month intervention period and at the 12-month follow-up with respect to childcare quality and children’s mental health, development, and well-being.

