## Results

### Trial Status

As of August 2020, in total, 1531 children and 769 staff from 187 toddler groups have been recruited. Due to turnover, staff recruitment will be ongoing until August 2020. As of January 2020, the intervention group has been working with Thrive by Three for 1.5 years. Data collection at T1, T2, and T3 from both the intervention and control groups has been completed and T4 will be completed in August 2020. We expect to find an increase in childcare quality and better mental health and development outcomes for children in the intervention group. The reporting of these results will be made in accordance with the CONSORT guidelines [45]. The trial began recruitment in February 2017 and finished in August 2018. Data collection will finish in August 2020.

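### Superiority over the wait-list control is hypothesized at the 12-month follow-up (T4), when the control centers are having or finishing the intervention and CLASS is observed in one arm only

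*Protocol article*

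**What the plan says.** **Hypothesis and aims.** The Study Hypothesis section defines the comparison as intervention centers against "wait-list control centers receiving the intervention 12 months later". It then predicts that the program will be "superior to the wait-list control after the 10-month intervention period and at the 12-month follow-up", for childcare quality and for children's mental health, development and well-being. The primary aims at the end of the Background section name the same two time points: "after the intervention and at a 12-month follow-up".

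**Control arm.** The Control section states: "The wait-list control group is offered the intervention 1 year later". It lists control observation at T1, T2 and T3 only. Eligibility Criteria likewise puts the control group's offer in the next year cycle. Table 1 marks that intervention in fall 2019 and spring 2020.

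**Timing of T4.** Data Collection places T3 in May/June 2019 and defines the last assessment as "T4 (1-year postintervention follow-up". Table 1 puts it in spring 2020, and Trial Status expects it to be complete in August 2020.

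**What is measured at T4.** Data Collection says that units are observed with CLASS "during a follow-up 1 year later (only the intervention group"), and the Childcare Quality section repeats the restriction. T4 questionnaires go to staff and parents with no restriction by arm. The Procedure overview, by contrast, has every unit observed "preintervention, midintervention, and postintervention and at 1-year follow-up", and Table 2 marks CLASS at T4 without naming an arm.

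**The concern.** A superiority claim at a given time needs a comparator that is measured at that time and has not had the treatment. At T4 the controls lack the second property for every outcome, and for CLASS they lack both.

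Two misreadings become possible. A small or null T4 difference on the questionnaires could be reported as fade-out of the effect, when the control children and staff had simply received the program in the meantime. And a CLASS level in the intervention arm that stays above baseline could be reported as a sustained program effect, although nothing in the data separates it from time trend, staff turnover or observer drift. The persistence of benefit is one of the two time points in the hypothesis, so the reporting of the main results is affected.

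**Working it through.** **1. Timeline.**

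| Event | Date | Source |
|---|---|---|
| Intervention arm treated | Fall 2018 and spring 2019 | Table 1 |
| T3 | May/June 2019 | Data Collection |
| Control arm treated | Fall 2019 and spring 2020 | Table 1; Control; Eligibility Criteria |
| T4 | Spring 2020, complete August 2020 | Table 1; Trial Status |

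T3 plus 12 months is May/June 2020. That is the end of the control arm's intervention year, so at T4 the controls are in the program or have just finished it.

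**2. Comparator at T4, by outcome.**

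| Outcome | Control data at T4 | What a T4 contrast would estimate |
|---|---|---|
| CLASS | None (Control, Data Collection, Childcare Quality) | No between-arm contrast |
| STRS-SF, LECP | Staff questionnaires, both arms | Earlier versus later start |
| BITSEA, C-TRF, CBCL, LDS, LICW-D, SBSHO | Staff and parent questionnaires, both arms | Earlier versus later start |

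**3. The plan's own sample size.** Inputs from Sample Size and Power: d = 0.30, power 0.80, α = 0.05 (two-sided assumed), 16 children per center, ICC 0.05 or 0.10, 20% missing.

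- A two-sample t-test needs 350.8 in total, so 176 per arm, 352 in all.
- Design effect 1 + 15 × ICC = 1.75 or 2.5, giving 352 × 1.75 = 616 or 352 × 2.5 = 880.
- 880 / 0.80 = 1100, and 1100 / 16 = 68.75, so 69 centers.

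All the stated figures reproduce. They assume an untreated control.

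**4. Illustration of attenuation at T4.** Suppose that controls have gained a fraction f of the effect and that the intervention arm keeps all of it with no further gain. The expected difference is then 0.30 × (1 − f). With 1100 × 0.80 = 880 children analyzed, the effective sample size is n_eff = 880 / 1.75 = 503 (ICC 0.05) or 880 / 2.5 = 352 (ICC 0.10). Power ≈ Φ(d × √(n_eff / 4) − 1.96).

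| f (assumed) | Expected d | Power, ICC 0.05 | Power, ICC 0.10 |
|---|---|---|---|
| 0 | 0.300 | 92% | 80% |
| 0.25 | 0.225 | 71% | 56% |
| 0.50 | 0.150 | 39% | 29% |
| 0.75 | 0.075 | 13% | 10% |
| 1 | 0 | 5% (α) | 5% (α) |

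Worked example, f = 0.50 and ICC 0.10: 0.15 × √88 − 1.96 = 1.407 − 1.96 = −0.553, and Φ(−0.553) = 0.29.

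The document gives no value for f, so the table shows only how the contrast responds to control treatment. The finding rests on steps 1 and 2.

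**The case against.** **A T4 comparison does exist for most outcomes.** A reader might infer that T4 offers no between-arm comparison at all. The documents do not support that. Questionnaires go to staff and parents in both arms, and every primary measure other than CLASS is questionnaire-based, including two of the three childcare-quality measures. Randomization still protects the T4 contrast. This objection stands and limits the point: only CLASS has no comparator. For the rest, the contrast is between two start dates.

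**The crossover is disclosed.** The delayed offer is stated several times, including in the definition of the comparison, and the Limitations section concedes incomplete long-term follow-up and speaks of following the intervention group. That is fair, but it describes maintenance within one arm. It does not withdraw the superiority claim at 12 months, and it sits poorly beside it.

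**Adjustment for child age.** Planned Statistical Analysis uses age to account for differing exposure. An age covariate does not supply an untreated control at T4.

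**The size of the loss is unknown.** This is correct. Control centers are offered the program and uptake is not reported. A second year might add benefit in the intervention arm. Recruitment reached 1531 children against 1100 planned. The stated 80% power is not tied to T4. The power table therefore cannot be read as a forecast.

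**Duration of the program.** A reader might also infer from Trial Status, where "the intervention group has been working with Thrive by Three for 1.5 years" as of January 2020, that delivery did not stop at 10 months and that T4 is not postintervention. The remark may mean only time elapsed since fall 2018, or continued practice after formal delivery. The two years mentioned under Planned Statistical Analysis describe how long some children stay in intervention classrooms. Neither establishes a longer program.

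**Conclusion.** The point holds. The T4 half of the superiority hypothesis contradicts the protocol's own schedule.

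- **CLASS:** a between-arm comparison at T4 is impossible, because no control unit is due to be observed.
- **Questionnaire outcomes, including STRS-SF and LECP:** a randomized contrast is available at T4, but it is earlier versus later start. It is likely attenuated and does not test the program against an untreated control. The amount of attenuation cannot be derived from the document.

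The conclusion assumes that Table 1's timing was followed and that at least some control centers accepted the offer. The CLASS part needs neither assumption. It needs only that the explicit restriction in Data Collection and Childcare Quality governs over the unrestricted wording in the Procedure overview and Table 2. The T3 comparison is untouched. A claim that the whole 12-month hypothesis is unanswerable, or that power at T4 falls to a specific figure, would go beyond the documents.

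**What to change.** 1. In Study Hypothesis, limit superiority over the wait-list control to T3, the end of the 10-month intervention.
2. In the primary aims (end of Background), word the 12-month aim to match, as maintenance and as early versus delayed start.
3. Report T4 CLASS as a within-arm description of maintenance, and state that it has no comparator.
4. Label all T4 questionnaire comparisons, including STRS-SF and LECP, as early versus delayed start. State in advance that a null difference will not be read as fade-out.
5. Reconcile the Procedure overview and Table 2, which do not restrict T4 CLASS by arm, with Control, Data Collection and Childcare Quality, which do.

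The cost is a change of wording in the protocol and in any analysis plan, with no new data. The price in substance is that the long-term superiority claim is given up. A T4 analysis restricted to children who left toddler groups before the control arm's intervention is not needed for this repair. It would rest on an undocumented assumption about where the 2019–20 delivery took place, and it gives no rule for LECP, which describes the group.
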